## Abstract

Osteoarthritis (OA) knee is one of the most common chronic degenerative conditions that imposes clinical and economic burdens on individuals and societies worldwide. Previous studies showed vitamin D levels correlated positively with lean muscle mass and grip strength, implying that vitamin D supplementation may improve muscle health in knee OA subjects. This randomized controlled trial (RCT) aims to compare the effects of vitamin D supplementation on knee muscle strength, physical function, pain, and sarcopenia status in patients with end-stage knee OA. Patients and outcome assessors will be blinded to group allocation. Fifty-six end-stage knee OA patients with vitamin D insufficiency fulfilling our inclusion criteria will be invited to participate in this study. Patients will be randomly assigned to take vitamin D supplementation (4,000 IU capsule daily) or placebo for six months. Measurements will be taken at baseline, three and six-month after the commencement of the vitamin D supplement, and 6-month after the interventional period. The primary outcome includes the isometric quadriceps and hamstring muscle strength measured by a hand-held dynamometer. Secondary outcomes include pain, performance-based and self-reported physical function and sarcopenia status. The success of this study will provide scientific evidence of whether the relatively cheap and well-tolerated vitamin D supplement can improve quadriceps muscle strength, physical function, pain symptoms, and sarcopenia status of this increasingly large population for end-stage knee OA patients. The study has great clinical significance given Hong Kong’s lengthy and growing waiting list for complete knee replacement procedures.

**Trial registration:** The trial was registered on clinicaltrials.gov (NCT05981534) on 31^st^ July 2023.

## Introduction

One of the most prevalent chronic degenerative disorders is osteoarthritis (OA) of the knee. Older adults who experience it become disabled, causing discomfort and stiffness. Among persons over 60, the prevalence of radiologic knee OA was 37.4%, while that of symptomatic knee OA was 12.1% [1]. With just 4300 total knee replacements conducted in 2021, the Hospital Authority (HA) had over 26,000 patients on its waiting list for knee total knee replacements (TKRs), meaning that the estimated waiting period in Hong Kong was about 89 months [2]. The number of people with end-stage knee OA who are waiting for surgery is anticipated to rise sharply as the population ages. While waiting for TKR, patients with end-stage OA can benefit from additional therapies to help them function better and maintain overall health.

Patients with end-stage knee OA frequently give up on physical activity to prevent joint stiffness and pain, which can negatively impact overall muscle health and localized knee function. As people age and become less active, their muscular mass and strength gradually decrease to an unusually low level known as "sarcopenia" [3]. Older adults with sarcopenia are more likely to have a decline in functional outcomes and a greater death rate, which puts a strain on their finances and healthcare system [4]. On the other hand, sarcopenia was found in 32.8% of patients with end-stage knee OA in a previous study on the prevalence of sarcopenia in end-stage knee OA patients. These patients likewise recovered more slowly following TKR [5]. A recent study categorized “sarcopenic knee OA” patients as a new subgroup with a higher risk of falling and associated risk factors than patients with sarcopenia or knee OA alone [6]. Strengthening exercise has been indicated to improve muscle mass, strength, and gait speed among sarcopenic patients [7]. However, the individual responses to exercise are variable [8].

The common therapies for knee OA include non-pharmacologic, pharmacologic, surgical, and intra-articular routes or the combined treatment to reach the optimal outcomes [9]. The initial treatment line for all OA stages is always non-pharmacologic and includes patient education, self-management, exercise and physical activity [10]. Pharmacologic interventions, such as NSAIDs, are required when OA worsens, and symptoms such as pain and stiffness become more severe [11]. For end-stage knee OA patients, total knee replacement surgery is one of the most effective surgical interventions for pain relief and functional recovery [12]. Other therapies, such as functional biomaterials and injectable hydrogel microspheres, that target improving the self-repair ability of articular cartilage have recently shown great therapeutic potential in the animal testing stage [13, 14]. Applying microenvironment-responsive nanosystems in OA treatment also has significant promise as a forward-thinking strategy for creating sophisticated therapeutic interventions, emphasising their potential to provide targeted and controlled drug delivery [15]. It offers valuable information on the development of nanosystems for improved treatment outcomes.

Although the benefits of vitamin D on musculoskeletal health have long been known, its impact on muscular function is also receiving more and more attention. By acting on certain vitamin D receptors in myocytes, vitamin D directly influences muscle growth. It has been observed that individuals with adequate vitamin D levels have larger, more numerous, and stronger muscular fibers. Additionally, vitamin D has positive benefits through its interaction with myokines such irisin and myostatin. Biological, clinical, and epidemiological data indicate the link between vitamin D and an elevated risk of sarcopenia in the elderly. It has been demonstrated that elderly patients with vitamin D deficiency are prone to sarcopenia [16]. In addition to having a negative effect on cartilage thickness, low blood vitamin D has been linked in a research to accelerated radiographic knee OA development [17]. Up to 62% of older adults with OA were found to have vitamin D insufficiency [18], and the risk of low vitamin D is exceptionally high compared to the average population, as many of these patients are confined indoors due to the decreased mobility limited by pain [19]. Thirty-six percent of Chinese adults over 65 who were evaluated had vitamin D deficiency (25(OH)D <20 ng/mL) [20]. According to the findings from previous systematic review, vitamin D supplementation can help people with knee OA with their pain and function [21]. In addition, those with end-stage knee OA would experience increased discomfort, which could result in reduced mobility, an increased risk of sarcopenia, and a vitamin D deficiency that needs to be addressed.

### Objectives

The study aims to investigate the effect of vitamin D supplementation on knee muscle strength, physical function, pain symptoms, and sarcopenia status in end-stage OA knee patients.

## Materials and methods

### Criteria, study timeline, ethics approval, consent form, clinical registration

The Standard Protocol Items: Recommendations for Interventional Trials (SPIRIT) criteria are adhered to by this protocol (see the SPIRIT checklist in S1 File) [22]. Fig 1 shows the SPIRIT schedule of enrolment, intervention, and assessments.

**Fig 1 pone.0309610.g001:**
[figure not shown]
SPIRIT schedule of enrolment, intervention, and assessments. This figure includes participants’ recruitment, allocation, intervention, and outcome assessments.

Initial ethics approval and consent to participate have been obtained from the Joint Chinese University of Hong Kong–New Territories East Cluster Clinical Research Ethics Committee (CREC no. 2022.252), in accordance with the declaration of Helsinki (See S2–S4 Files with initial ethic approval, the updated ethics approval, Chinese and English versions of consent forms, and approved protocol). The trial was registered on clinicaltrials.gov (NCT05981534).

All participants will be required to provide written informed consent prior to enrollment. The informed consent process will be conducted by a trained research staff member, who will explain the study purpose, procedures, potential risks and benefits, and the participants’ right to withdraw from the study at any time without penalty. Participants will be given sufficient time to review the informed consent form and ask any questions they may have before signing.

#### Potential ethical concerns

*Risks of vitamin D supplementation*. While vitamin D supplementation is generally considered safe, there is a small risk of hypercalcemia or other adverse effects. Participants will be closely monitored. Any participants who develop significant adverse events will be withdrawn from the study and provided with appropriate medical care.

*The burden on participants*. The study involves multiple visits and assessments over 12 months, which may be burdensome for some participants. To mitigate this, participants will have flexible scheduling to accommodate their needs.

*Confidentiality and data protection*. All participant data will be de-identified and stored securely. Only the research team will have access to the identifiable data, and any publications or presentations will ensure participant anonymity.

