### Procedure for unbinding if needed

Unless a major unfavorable event happens, such as hypercalcemia or kidney stones, blindness will be kept in place under normal conditions. The trial’s unblinded participants will thereafter be terminated, and their medical issues will be treated appropriately.

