### Adverse events, safety and modifications

The upper tolerable intake level for vitamin D in the general population has been set at 4000/IU daily [26]; as this is a long-term treatment program, the self-reported harm effects remain uncertain. Research staff will monitor and handle participant concerns regarding discomfort. Medical staff will also evaluate whether immediate removal from the study is necessary for their best interest to safeguard their health. Any unfavorable incidents or adverse events that develop throughout the study will be brought to the attic committee.

A significant adverse event must be notified to the Hong Kong Hospital Authority Research Ethics Committee within twenty-four hours of the incident. Until the serious adverse event is resolved or finished, the primary investigator will be in charge of managing it. The trial steering group and investigators will determine whether a minor or significant adverse event is related to the study intervention. The principal investigator will promptly stop the intervention if the reported event is connected to it and advise the patient to seek medical attention.

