### Adherence and satisfaction

Patients will be required to keep personal diaries with information on their medications. Additionally, the study team will increase adherence by calling the patients once a week to check on them. The research staff will contact patients who miss a scheduled session and ask them to reschedule at a different time within a week. When a patient refuses to participate in the study, the researchers will only withdraw them from it after making several unsuccessful attempts to get in touch with and persuade them. Participants can also stop participating in the study at any time for any reason; if they do, they will be asked if they want to be contacted again according to the trial schedule. Participants will be encouraged to report the incidence of falls in the study period.

Satisfaction and feedback will be recorded based on the following questions at 0-month, 3-month, 6-month and 12-month follow-up assessments.

Are you satisfied with the vitamin D supplementation? (1 = Very Dissatisfied, 2 = Dissatisfied, 3 = Neutral, 4 = Satisfied, 5 = Very Satisfied)How effective do you feel the vitamin D supplementation has managed your knee osteoarthritis symptoms? (1 = Not effective at all, 2 = Slightly effective, 3 = Moderately effective, 4 = Highly effective, 5 = Extremely effective)Do you have any additional comments or feedback regarding your experience with the vitamin D supplementation?

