### Statistical analysis

Data in this study will be analyzed according to the intention-to-treat principle. Only the full analysis set and per-protocol set will be used for primary outcome analysis. The last observation carried forward (LOCF) will be used to impute the missing data by replacing it with the last observed value.

Quantitative variables will be expressed as mean ± standard deviation. Normality tests will be performed to determine whether the data is normally distributed. A one-way analysis of covariance (ANCOVA) tests with Bonferroni correction and with the baseline value as a covariate was conducted at 3m,6m, and 12m to determine the group effect on each parameter. Independent T-test (two-tailed) are used for multiple testing of continuous variables. Whereas the Chi-square test will be used to compare the proportions of categorical variables and to calculate the differences in the count data. A repeated measure analysis of variance (ANOVA) will be used to analyze the trend of changes in the scores among four-time points (Baseline, 3m, 6m, 12m) to determine the group×time effects. Post hoc analysis with Bonferroni correction will be conducted to explore the differences between baseline and 3m, baseline and 6m, 6m and 12m. The statistical analysis will be performed using commercialized statistical software (SPSS, version 29.0, IBM). All statistical significance is defined as P < 0.05.

Additional analyses will include subgroup analyses to estimate treatment effects for both female and male participants, normal BMI and overweight or obese participants.

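### Two sections take patients out of the study after a significant adverse event or code break, partly against the safety section; followed literally, willing patients' later outcomes become LOCF values

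*Protocol article*

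**What the plan says.** All references are to the protocol article.

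- **Potential ethical concerns**, in the paragraph on supplement risks, expects few events ("there is a small risk of hypercalcemia or other adverse effects") and then sets the rule: "Any participants who develop significant adverse events will be withdrawn from the study and provided with appropriate medical care".
- **Procedure for unbinding if needed** allows the code to be broken for a major event, with hypercalcemia and kidney stones as examples. It adds that the trial's "unblinded participants will thereafter be terminated, and their medical issues will be treated appropriately".
- **Adverse events, safety and modifications** makes removal a judgement: "Medical staff will also evaluate whether immediate removal from the study is necessary for their best interest to safeguard their health". For an event judged related it says: "The principal investigator will promptly stop the intervention if the reported event is connected to it".
- **Adherence and satisfaction** lets people leave by choice, whenever and for whatever cause, and makes these leavers an offer: "if they do, they will be asked if they want to be contacted again according to the trial schedule".
- **Statistical analysis** adopts the intention-to-treat principle and adds: "The last observation carried forward (LOCF) will be used to impute the missing data by replacing it with the last observed value".

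**The concern.** Stopping the study drug and leaving the study are different events. An intention-to-treat analysis wants outcomes from every randomized patient, including those who stopped capsules early. A rule that takes a patient out of the study because of an adverse event or a code break gives up measurements that the patient might have been willing to provide.

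The losses would not be a random subset. Hypercalcemia and kidney stones can be effects of vitamin D, so removals may be more frequent in the active arm. Under the stated method each lost visit is then filled with an earlier reading. The protocol would be creating informative missing data that it could avoid, and then imputing over it. Medical care for these patients is not in question.

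**Working it through.** **1. The rules side by side**

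| Section | Trigger | Automatic or judged | What ends |
|---|---|---|---|
| Potential ethical concerns | Any significant adverse event, related or not | Automatic | Being in the study |
| Procedure for unbinding if needed | Code break after a major event | Automatic | Unclear; most naturally participation |
| Adverse events, safety and modifications | Participant discomfort and health concerns | Judged by medical staff | Possibly being in the study |
| Same section | Event judged related | Automatic once related | The intervention |
| Adherence and satisfaction | Patient's own choice | Patient decides | Participation, with an offer of further contact on schedule |

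The first row and the third and fourth rows cannot both be followed in every case. Take a significant but unrelated event after which the patient is fit to continue and wishes to. The first row removes that patient. The safety section would have staff judge the matter and would not require the capsules to stop. The offer in the last row covers patients who choose to stop after an event. It is not extended to patients whom the study removes.

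**2. What follows in the analysis**

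If removal ends the visits, the later values are missing and LOCF supplies them. The substitute depends on timing:

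- Removed before month 3: months 3, 6 and 12 all take the baseline value, so change is recorded as zero three times.
- Removed between months 3 and 6: months 6 and 12 take the month-3 value.
- Removed between months 6 and 12: month 12 takes the month-6 value.

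The last case shows the problem most plainly. Capsules are taken for six months and the final visit comes six months later. Removal for an event in that period stops no study drug, yet read literally it still costs the 12-month measurement.

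**3. How much data one patient represents**

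Inputs: 28 patients per arm (Randomization and allocation concealment) and three post-baseline visits (Outcomes and outcome assessments).

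- Share of an arm: 1/28 = 3.6%.
- Post-baseline values per arm for one outcome: 28 × 3 = 84.
- Replaced per removed patient: 3/84 = 3.6%, 2/84 = 2.4% or 1/84 = 1.2%, in the order of timing above.

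For scale only, assume 1 to 3 removals in one arm before month 3. That replaces 3/84 = 3.6% to 9/84 = 10.7% of the arm's values. The protocol gives no event rate, so these counts are not a forecast.

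**4. Direction**

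If a removed patient would have gained strength, carrying the baseline forward understates that patient's outcome. If the illness would have reduced strength, it overstates it. Carrying a month-6 value to month 12 assumes that nothing changes after the capsules stop. Nothing in the document settles which case dominates, so no bias estimate is given.

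**The case against.** The strongest case against is that the harm is inferred. No sentence says that assessments cease. The word used after unblinding could mean that treatment ends, and the ethics paragraph is a short reassurance, while the section on adverse events is the operative one. That section itself allows removal, so the conflict is only partial. The approved protocol is in supplementary files not shown here, and an article may condense how removed patients are followed. All of this limits the point. It does not remove it, because the ethics paragraph states a rule, in terms of the study and not the capsules. If only the capsules were meant, the sentence is wrong as written.

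Four stronger readings are tempting and unsupported:

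- *The protocol expressly ends assessments for these patients.* It does not; this is the literal consequence of its removal wording.
- *The safety section already guarantees continued follow-up.* It names stopping the intervention for a related event and is silent on later visits.
- *Each removal uses up one of the 28 − 23 = 5 places per arm allowed for attrition.* LOCF keeps the patient in the analysis, so that count does not describe this mechanism.
- *A definite dilution of the effect or loss of power follows.* That would need an event rate and the gap between carried and true values, and neither is given.

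One objection to the remedy also stands. The primary outcome is a maximal voluntary effort and several secondary outcomes are self-reported, so patients who learn their arm may respond differently. Retained values after a code break are therefore not free of bias.

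**Conclusion.** The point holds as a partial contradiction with an avoidable consequence. One section withdraws patients automatically after any significant adverse event, and another most naturally ends participation after unblinding. The safety section leaves removal to judgement and, for a related event, names only the intervention as stopping. Followed literally, the first two rules exchange obtainable outcomes for carried-forward ones in patients whose events may be drug-related.

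The effect is probably confined to a few patients, each 3.6% of an arm with at most 3 of 84 post-baseline values per outcome. The size and direction of any bias are unknown. The conclusion rests on two assumptions: that withdrawal from the study includes its visits, and that some of these patients would be willing to attend. It is worth correcting because the remedy is cheap and lost visits cannot be recovered. Whether LOCF is a suitable method, and the inconsistent statements on assessor blinding, are separate questions on which this point does not depend.

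**What to change.** Reword Potential ethical concerns and Procedure for unbinding if needed, and bring Adverse events, safety and modifications into line, along these lines:

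> After a significant adverse event or a code break, medical staff decide whether the study capsules are stopped. Neither event by itself ends participation. The participant is asked whether they will attend the assessments that remain at 3, 6 and 12 months. Measurements from those who agree are used in the intention-to-treat analysis.

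Patients keep the right to leave, and medical staff keep the power to end participation where attendance itself would be unsafe. Values obtained after a patient has learned their arm should be flagged, and a sensitivity analysis can check their influence.

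The cost is a protocol amendment through the ethics committee while recruitment is under way, plus a few visits already in the schedule. No new procedure is needed. The remaining downside is the possible expectation effect in unblinded patients, which the flag and sensitivity analysis make visible but do not remove.

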### Trial design

The study is a randomized, double-blinded, controlled study that aims to compare the effects of vitamin D supplementation on knee muscle strength, physical function, pain, and sarcopenia status in patients with end-stage knee OA at 3 months and 6 months after the commencement of vitamin D supplement, and 6-month after the interventional period.

### Participants and setting

Based on our inclusion criteria, participants will be recruited with consent from the outpatient clinic of the Department of Orthopaedics and Traumatology at the Prince of Wales Hospital (affiliated with the Chinese University of Hong Kong).

### Eligibility criteria

To be enrolled in this trial, the following eligibility criteria, assessed at screening, will be met:

#### Inclusion criteria

The inclusion criteria are as follows:

Male and female patients aged over 50 and clinically diagnosed with knee OA with Kellgren-Lawrence (KL)grade 3 or above at least one side.Patients are on the waiting list for TKR at Prince of Wales HospitalWalk unaided for 6 metersAble to comply with the assessments and has given oral and written consentPatients with vitamin D insufficiency and deficiency at the baseline measurement (25(OH)D <30 ng/mL)

